Based on the context outlined and considering that there is insufficient evidence using a physiotherapeutic intervention protocol associated with Kangaroo Position in neonatal units, some questions arise: a) Is the combination of a physiotherapeutic protocol with Kangaroo Position more effective in improving clinical outcomes, including body weight, breastfeeding, behavioral state, length of hospital stay? b) Is the combination of a physiotherapeutic protocol with Kangaroo Position more effective in improving posture and tone, and normalizing general movements, in newborns with poor motor repertoire than Kangaroo Position alone?

Considering the evidence that early intervention (SYMINGTON; PINELLI, 2016) and Kangaroo Position (NUNES et al., 2017) improve self-regulation and the mother-infant bond, it is hypothesized that the application of the physiotherapeutic intervention protocol associated with Kangaroo Position over fifteen days in stable preterm newborns hospitalized in a neonatal unit will lead to an improvement in clinical outcomes while safely maintaining vital signs. As a consequence, and based on the beneficial effects of Kangaroo Position (SANTOS; FILHO, 2016) and early intervention (MARLOW, 2004) on body posture, muscle tone, and spontaneous movement, it is expected that these newborns will show better motor patterns immediately after the protocol, and at 12 weeks post-term, compared to control newborns.

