### **4.3 Inclusion criteria**

Preterm newborns will be included in the study if they meet the following criteria: gestational age at birth equal to or less than 34 weeks, more than 72 hours of postnatal life, hospitalized in the Neonatal Intermediate Care Unit (UCIN), clinically stable, general

movements with a poor repertoire, no need for invasive or non-invasive mechanical ventilation, may require oxygen support via nasal cannula, residents of Campo Grande-MS (Brazil).

Medical records, nursing notes, physiotherapy records, and the recommendations from neonatologists and the multidisciplinary team will be used as the reference for the selection or exclusion of patients based on the criteria described above.

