#### **4.4 Exclusion criteria**

Preterm newborns will be excluded from the study if their gestational age at birth is equal to or greater than 34 weeks and 1 day, or if they have any of the following conditions: congenital malformations, chromosomal syndromes, active infections under treatment (with altered blood count or positive blood culture), neurological problems (such as grade III or IV intraventricular hemorrhage or brain malformations), neonatal asphyxia (with an Apgar score of less than 7 at the fifth minute), or congenital infections. Additionally, newborns will be excluded if they have any contraindications to performing the physiotherapy intervention protocol or the kangaroo position.

They will also be excluded if their parents or guardians do not consent to the newborn's participation in the study or request their withdrawal. If the newborn experiences adverse reactions to the physiotherapy protocol or kangaroo positioning, such as clinical instability during the procedure (e.g., cyanosis, crying, lethargy, signs of pain, generalized erythema) or in the short and medium term (e.g., worsening of the clinical condition, feeding intolerance, or behavioral disturbances), they will be excluded. Moreover, newborns may also be excluded if complications arise that prevent the application of the protocol, such as the need for invasive or non-invasive mechanical ventilation, oxygen therapy via a Hood Box, or the requirement of surgical procedures.

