#### 4.7.3 Brazelton's Neonatal Behavioral State

The adapted Brazelton's Neonatal Behavioral Assessment Scale was used to assess behavioral state. The scale categorizes the newborn's behavior based on their current state,

ranging from 1 to 6. State 1: deep sleep, still with steady breathing; State 2: light or active sleep, eyes closed with occasional body movements; State 3: drowsy, intermittently opening and closing the eyes; State 4: quietly alert, minimal physical activity; State 5: fully awake with energetic movements (active alert); State 6: crying (BRAZELTON et al., 1976).

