#### **4.8.2 Procedures of randomization and allocation**

The distribution of newborns into groups will be random, following a prior computational randomization in blocks of 4 babies for each group. The allocation to the groups will be concealed from the researchers involved through individual opaque, sealed, and sequentially numbered envelopes. The envelopes will be opened before the experimental or control protocol is performed, according to the inclusion of the babies in the study. The evaluations for GMs will be filmed and scored later, without identifying the allocation of the newborns in the groups, allowing for a subsequent blinded assessment.

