## 5. Risks and Benefits

This study presents no physical or psychological risks to the newborn; however, there may be signs of sensory overload such as: color fluctuations (paleness, perioral cyanosis, among others), cardiorespiratory changes (bradycardia, irregular breathing, apnea, irregular respiratory rate), changes in state (hiccups, yawning, salivation, startles, crying, irritability), and signs of withdrawal when the newborn is handled. If signs of overload are detected, the handling should be interrupted to allow the newborn to organize, using maneuvers such as positioning and firm touch.

As for the benefits, the research will provide early stimulation/intervention to hospitalized preterm newborns, enhancing the baby's interaction with the environment through sensory-motor stimuli, which the baby interprets as pleasurable (approach signals). The kangaroo position is a safe and low-cost intervention, which can be performed in any hospital and provides the multidisciplinary team with an important additional resource in the care and attention of preterm newborns and their families, making them active participants in the treatment and promoting an efficient transition from the hospital environment to the home environment.

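### Section 4.4 excludes infants for adverse reactions that occur after allocation, so the groups compared are no longer those randomised

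*Protocol*

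**What the plan says.** Section 4.4 opens with genuine baseline conditions (gestational age, malformations, infection, severe haemorrhage, asphyxia). Its second paragraph turns to events that arise during treatment:

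- **Mandatory.** "If the newborn experiences adverse reactions to the physiotherapy protocol or kangaroo positioning, such as clinical instability during the procedure" (cyanosis, crying, lethargy, pain signs and erythema are the examples), or a later reaction such as "worsening of the clinical condition, feeding intolerance, or behavioral disturbances), they will be excluded".
- **Discretionary.** "newborns may also be excluded if complications arise that prevent the application of the protocol", with ventilation, Hood Box oxygen and surgery as the examples.
- **Parental decision.** Refusal or withdrawal of consent sits in the same paragraph.

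Section 4.8.2 has the envelope opened before the assigned protocol is performed, so a reaction to a session always follows allocation. Section 4.8.5.1 gives the handling to the experimental group only. The control protocol section gives the control group the same kangaroo positioning. Section 4.10 says that the groups will be compared and does not say that excluded infants remain in the comparison.

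Section 5 (Risks and Benefits) describes overlapping signs, including crying and perioral cyanosis, and answers them differently: "If signs of overload are detected, the handling should be interrupted to allow the newborn to organize".

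**The concern.** Randomisation protects a comparison only while the infants analysed are the infants allocated. A rule that removes infants because of what happened under treatment undoes that protection, and more so when the arms differ in exposure to the trigger. Experimental infants can react to the handling or to the kangaroo position; control infants only to the latter. Section 4.8.2 describes blinding for the scoring of GM films only, so nothing indicates that the decision to exclude is made blind.

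Several triggers are also outcomes or lie close to them. Feeding intolerance bears directly on weight gain, a primary outcome, and on breastfeeding. Crying is a category of the behavioural-state outcome ("State 6: crying"). Cyanosis and instability bear on oxygen saturation and on the hypothesis in section 1 that the intervention works "while safely maintaining vital signs". Infants who do badly on these measures would leave the study because they do badly.

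An analysis plan cannot fully repair this. It could define an analysis set by allocation, but it cannot recover weights and 12-week films that were never collected because the protocol had taken the infant out.

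**Working it through.** **The plan's own figure.** Section 4.2 gives 13 per group for a 50% difference in GM quality (chi-square, 80% power, 5%), raised to 17 for losses. Assumptions: the difference is 50 percentage points, the test is two-sided, and there is no continuity correction. The control rate is not stated.

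n = [1.960 × √(2p̄(1−p̄)) + 0.842 × √(p₁(1−p₁) + p₂(1−p₂))]² / 0.5²

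- 0% v 50%: 11
- 5% v 55%: 12
- 10% v 60%: 14
- 25% v 75%: 15

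The stated 13 lies inside this range. The allowance is 17 − 13 = 4 per arm, or 4/17 = 23.5%. The protocol describes it as follow-up loss, not as an allowance for reactions.

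**GM illustration.** The documents give no reaction rate and no link between reactions and GM class, so the following are assumptions:

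- no true effect, and 17 per arm;
- the same normal-GM rate p in both arms, 30% to 50%;
- k = 3 or 4 infants removed, from the experimental arm only;
- uncorrected chi-square test at two-sided 5%, all outcomes enumerated exactly.

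If m of the k removed infants have abnormal GMs, the apparent difference is

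(17p − (k − m)) / (17 − k) − p.

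*Strong link (every removed infant abnormal, m = k).* This reduces to kp/(17 − k). For p = 0.3, k = 3: 0.9/14 = +6.4 points. For p = 0.5, k = 4: 2/13 = +15.4 points (+15.3 by enumeration, because a few simulated arms have fewer than 4 abnormal infants).

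*Mild link (at each removal an abnormal infant is twice as likely to be taken as a normal one).* For p = 0.3, k = 3, m averages 2.44: (5.1 − 0.56)/14 − 0.3 = +2.4 points. For p = 0.5, k = 4, m averages 2.57: (8.5 − 1.43)/13 − 0.5 = +4.4 points.

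Apparent difference in points, with the chance of a significant result favouring the experimental arm:

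| p | k | Mild link | Strong link |
|---|---|---|---|
| 30% | 3 | +2.4; 3.7% | +6.4; 6.2% |
| 30% | 4 | +3.4; 4.6% | +9.2; 9.5% |
| 40% | 3 | +2.9; 3.4% | +8.6; 7.6% |
| 40% | 4 | +4.0; 4.5% | +12.3; 11.5% |
| 50% | 3 | +3.2; 3.9% | +10.7; 10.5% |
| 50% | 4 | +4.4; 4.1% | +15.3; 15.4% |

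With nobody removed, the chance is 2.3% to 2.9% (nominal 2.5%). If one control infant is also removed against three experimental infants under the mild link, the difference is about +2 points and the chance about 3%. If removal is unrelated to GM class, the difference is zero.

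**Weight illustration.** Removing the lowest 1 to 4 gainers of 17 raises the experimental mean by 0.11 to 0.38 SD. If the correlation between reacting and poor gain is only 0.3 to 0.5, the shift is 0.03 to 0.19 SD.

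**The case against.** Several limits on the point stand.

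- **Control infants are also covered.** The rule names reactions to kangaroo positioning, which both arms receive. A reader might infer that only experimental infants can be lost; the text does not say so. What remains is one additional exposure in the experimental arm, hence an expected direction without a known size.
- **Not every event forces exclusion.** Ventilation, Hood Box oxygen and surgery carry discretionary wording.
- **The upper end of the GM range is a worst case.** It needs every removed infant to be abnormal and no control removals. Nothing in the protocol ties reactions to GM class, so bias on GMs is inferred.
- **Vital signs.** A reader might infer that safety would be judged only in infants who tolerated the sessions. Section 4.8.4.1 records vital signs three times daily, and nothing says that values taken before exclusion are discarded. The loss is of what follows the exclusion, and possibly of the infant from the comparison.
- **Sections 4.4 and 5 do not flatly contradict each other.** Section 5 concerns sensory overload and is silent on exclusion; interrupting a session and later excluding the infant could coexist. The shared signs still leave it unclear which response applies.
- **Late scoring.** Poor repertoire is an inclusion criterion ("movements with a poor repertoire"), and section 4.8.2 says "The evaluations for GMs will be filmed and scored later". A reader might infer that infants are randomised before eligibility is known and then dropped. The text does not show this: the recruitment section takes in infants who already meet the criteria, the first GM assessment is the day before the sessions start, and the later scoring is described as serving blinded assessment.

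None of this restores the excluded infants. The mandatory rule is explicit, applies after allocation, and is not offset elsewhere in the protocol.

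**Conclusion.** The point holds. Followed as written, section 4.4 removes infants after randomisation for reasons that treatment can cause, and so breaks the randomised comparison. Excess removal from the experimental arm is the expected direction. The consequence is direct for weight gain, behavioural state and the vital-signs hypothesis, and plausible but unproven for GMs.

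Under the assumed 3-4 experimental removals, the GM effect ranges from about +2 to +4 points and 3-5% false significance in the experimental arm's favour, up to +6 to +15 points and 6-15%. The number removed, the normal-GM rate and the strength of the link are all assumptions. With 17 per arm, a few selective removals could matter, and follow-up never collected cannot be reconstructed.

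**What to change.** 1. In section 4.4, keep only conditions known before allocation as exclusion criteria.
2. For events after allocation, separate discontinuing the assigned sessions from leaving the study. Unless the parents withdraw consent, the infant continues to be weighed and assessed at the planned time points where feasible, and is analysed in the allocated group.
3. Count these events and report them by arm as a safety outcome.
4. Reconcile sections 4.4 and 5 on what follows shared signs such as crying and cyanosis. The clinical rule itself is for the investigators.

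The cost is protocol wording. Daily weight, length of stay and the 12-week GM film are already planned; the extra work is completing them for infants who would otherwise have left. Some assessments may be impossible for an infant who is ventilated or in surgery, hence the feasibility clause. The statistical price is a somewhat diluted effect if some infants do not complete the sessions.

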#### **4.5 Recruitment and data collection locations**

The newborns will be recruited from the Neonatal Intermediate Care Units (UCIN) at the Hospital Universitário Maria Aparecida Pedrossian (HUMAP) of the Universidade Federal de Mato Grosso do Sul (UFMS) and from the UCIN at the Hospital Regional de Mato Grosso do Sul (HRMS). During the hospitalization period, data collection will take place in the UCIN itself, and after discharge, at the Laboratório de Estudos em Neuropediatria (LABEN) at the Clínica Escola Integrada of UFMS or in the home environment.

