### **4.2 Participants**

This study will involve 34 preterm newborns, born with a gestational age of 34 weeks or less, between 34 and 36 weeks and 6 days postmenstrual age, hospitalized in the Neonatal Intermediate Care Unit (UCIN). To estimate the minimum number of participants, considering a difference of at least 50% between the groups regarding the quality of general movements (GMs) after the intervention using the chi-square test, the suggested sample size is 13 participants per group (80% power;  $\alpha = 5\%$ ). Considering potential losses during the follow-up, two groups of 17 participants will be included. The newborns will be randomly allocated into two groups: the experimental group ( $n=17$ ), which will receive the physiotherapy intervention protocol associated with the kangaroo position, and the control group ( $n=17$ ), which will receive only the kangaroo position.

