#### **4.9.2 Secondary outcomes**

- **Posture and Muscle Tone:** behavior regarding posture and muscle tone, assessed by the classification achieved using the neurological signs evaluation method from the neonatal neuromotor screening (GONÇALVES, 2012).
- **Behavioral State:** Behavioral state according to the adapted Brazelton scale (BRAZELTON et al., 1976).

- **Time to Establish Breastfeeding:** defined as the interval in days between the start of the protocol and successful breastfeeding at the breast. Success in breastfeeding will be considered according to the main key points for proper positioning and latch during the feeding: the baby's face facing the breast, with the nose at nipple level, the baby's body close to the mother's, with the baby's head and torso aligned; the baby well supported; more areola visible above the baby's mouth; mouth wide open; lower lip turned outward; and the chin touching the breast (BRASIL, 2011a).
- **Exclusive Breastfeeding Maintenance:** defined as the continuation of exclusive breastfeeding at corrected ages of 2 weeks post-term, 12 weeks post-term, and at 6 months, being dichotomous.
- **Hospitalization Time:** defined as the average number of days the newborn stays in the hospital environment.
- **Degree of Respiratory Distress** obtained by summing the score according to the BSA (SILVERMAN; ANDERSEN, 1956; BRASIL, 2011b) on each day of the protocol.
- **Physiological Parameters** (heart rate, respiratory rate, peripheral oxygen saturation, body temperature): vital signs evaluated and recorded before and after the protocol (experimental and control) each day.

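### Two hospitals recruit, but section 4.8.2 states no stratification by hospital and no test in 4.10 includes it; this is a cheap loss of precision, not a bias

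*Protocol*

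**What the plan says.** **Recruitment.** Section 4.5 states "The newborns will be recruited from the Neonatal Intermediate Care Units (UCIN" of two hospitals: the university hospital and "from the UCIN at the Hospital Regional de Mato Grosso do Sul (HRMS". The section on relevance and feasibility also names both. Section 2 (Justification) mentions only the university hospital.

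**Allocation.** Section 4.8.2 describes the sequence as "following a prior computational randomization in blocks of 4 babies for each group", concealed in "individual opaque, sealed, and sequentially numbered envelopes". It does not mention hospital as a stratum, and it does not say whether there is one list and envelope series or one for each hospital. Section 4.2 sets the size: "two groups of 17 participants will be included".

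**Analysis.** Section 4.10 compares the arms with a chi-square test for categorical outcomes, an independent t-test for body weight, and t or Mann-Whitney tests for the other continuous outcomes. An optional mixed model names only group-by-day terms. Hospital appears in none of these.

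**Outcomes most likely to follow local practice.** Weight gain is a primary outcome (section 4.9.1). Time to establish breastfeeding, exclusive breastfeeding and hospital stay are secondary (section 4.9.2); stay is "defined as the average number of days the newborn stays in the hospital environment".

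**The concern.** Permuted blocks on one list keep the arms level overall, but not within each hospital. With 34 infants, one arm can by chance receive noticeably more infants from one unit. A unit's feeding and discharge practice can plausibly affect how fast an infant gains weight, when breastfeeding is established and when the infant goes home. If the two units differ in these respects, a chance imbalance moves the observed arm difference in the trial at hand. Even without imbalance, the hospital difference stays in the error term of an unadjusted test.

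The allocation part belongs in the protocol. An analysis plan can add a covariate later, but it cannot stratify a sequence that is already in use.

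**Working it through.** **Inputs.** From the protocol: 34 infants, 17 per arm (4.2); two hospitals (4.5); blocks of 4 (4.8.2). Not in the protocol, so assumed: the hospital split, random order of arrival from the two units, one common list, and any outcome difference between hospitals.

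**1. The plan's own figure.** Section 4.2 assumes "considering a difference of at least 50% between the groups regarding the quality of general movements (GMs) after the intervention using the chi-square test" and concludes that "the suggested sample size is 13 participants per group (80% power" and a 5% significance level apply. The usual formula is n = [1.96·√(2·p̄(1−p̄)) + 0.842·√(p₁(1−p₁) + p₂(1−p₂))]² / (p₁−p₂)². For 10% against 60%, p̄ = 0.35 and n = (1.322 + 0.483)² / 0.25 ≈ 13.0. Rounded up, n runs from 11 to 15 per group over control rates from 0 to 50%, so 13 is reproduced within 2. A 20% loss gives 13/0.8 = 16.25, rounded up to 17. The point made here does not change this number.

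**2. Imbalance within a hospital, one common list.** Simulation of 34 infants, with hospital assigned at random:

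| Hospital split | Block size | Arms differ by ≥4 in a hospital | By ≥6 |
|---|---|---|---|
| 50:50 | 4 | 28% | 8% |
| 30:70 | 4 | 24% | 5-6% |
| 50:50 | 8 | 30% | 9% |
| 30:70 | 8 | 26% | 6% |

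The rows for blocks of 8 cover the other reading of the block wording (4 babies in each group). With a separate list in blocks of 4 for each hospital, both probabilities are zero.

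**3. The same as shares.** Let D be the difference between arms in the share of infants from hospital 1. The mean of D is 0. With one list in blocks of 4:

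| Infants per hospital | P(\|D\| ≥ 20 points) | P(\|D\| ≥ 30 points) | 95th percentile of \|D\| |
|---|---|---|---|
| 17/17 | 22% | 5% | 35 points |
| 22/12 | 24% | 7% | 35 points |
| 27/7 | 13% | 2% | 29 points |

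Separate lists in blocks of 4 reduce the 95th percentile to 4-6 points and the chance of 20 points or more to zero.

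**4. From imbalance to outcome.** Shift in the arm contrast = D × difference between hospitals. With 17 per arm, a within-hospital difference of d infants gives D = d/17, so 4/17 = 0.24 and 6/17 = 0.35. If stay differed by 5 days between hospitals (assumption), the shifts are 0.24 × 5 = 1.2 days and 0.35 × 5 = 1.8 days. For assumed differences of 3, 5 and 10 days and a 17/17 split, the simulated 95th-percentile shift is about 1.1, 1.8 and 3.5 days.

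**5. Precision.** Let the hospitals differ by δ within-hospital SDs, split 50:50. Without adjustment the error variance is about 1 + δ²/4. For δ = 1 this is 1.25, an SD of 1.118, so a true effect of 1 SD becomes 1/1.118 = 0.894 SD. The t-test's non-centrality falls from √(17/2) = 2.92 to 0.894 × 2.92 = 2.61. Against a critical value of 2.04 (32 degrees of freedom), power is about Φ(0.88) = 81% and Φ(0.57) = 71-72%. Simulation agrees: with separate lists and a hospital term, power is about 81% when the hospitals do not differ, and it rises from about 71% to 80% when they differ by 1 SD.

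**The case against.** The strongest reply is that nothing here is biased or invalid. Each infant is randomised individually, so imbalance by hospital is pure chance, and unadjusted tests already allow for it in their error rate and confidence intervals. This stands. A reader might infer that hospital is confounded with arm, but the design does not support that. What remains is lost precision and an avoidable shift in an unlucky sequence.

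A reader might also take it as stated that one list serves both hospitals, and that one envelope series would have to travel between them. Section 4.8.2 says neither. A common list is the natural reading of a description that omits hospital, but separate series are not excluded, and moving envelopes would not in itself be a fault.

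The documents also give no enrolment split and no evidence that routines differ. Both units are of the same type, and all infants live in one city. The size of any shift in days or grams therefore rests on assumption.

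A hospital covariate could be specified in an analysis plan that is not shown, so its absence from section 4.10 is the weaker half of the point. The allocation half does not depend on that.

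Finally, leaving a trial of 34 unstratified is a defensible choice. Two strata with blocks of 4 are nevertheless easily carried by 34 infants.

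**Conclusion.** The point holds as a low-cost improvement. Section 4.8.2 fixes the allocation method for a two-hospital trial without mentioning hospital, and no stated test uses it. Expected bias is zero. If the list is common and infants arrive at random from the two units, the chance of an arm difference of 4 or more within a hospital is about 24-28%, and of 6 or more about 5-8%, for splits from 30:70 to 50:50. This matters for weight gain, breastfeeding and stay only so far as the hospitals differ in practice, which the documents leave open. If they do not differ, stratifying and adjusting leaves power at about 81%. If they differ by 1 SD, it recovers about 9 percentage points. The sample size and the validity of the planned tests are not in question.

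**What to change.** - **Section 4.8.2:** state that each hospital has its own computer-generated blocked list and its own numbered envelope series. If that is already the intention, one sentence is enough. Say also whether a block holds 4 infants in total or 4 per arm.
- **Section 4.10:** include hospital as a factor in the comparison of body weight and of the other continuous outcomes. Where a rank test is used, its hospital-stratified form (van Elteren) does the same job.

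**Cost.** Two lists instead of one, a variable that is known for every infant, and one degree of freedom. Each hospital may end on an incomplete block, so the total may miss 17:17. The loss is small: 34 = 8 × 4 + 2, so one common list in blocks of 4 can already end 18:16. With two lists, the infants left over in the last blocks number 0 and 2, 1 and 1, or 3 and 3, so the split is again no worse than 18:16. A fixed block of 4 within one unit is somewhat easier for unblinded staff to predict; undisclosed, varying block sizes would reduce that.
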